### Inclusion and exclusion criteria

The inclusion criteria are pregnant women with 18 years old or more; gestational age (GA) less than 20 weeks of gestation and antenatal care at the study setting. - The exclusion criteria is professional indication validated by a professor to individualize care (will be sent to the indicated professionals or sectors, e.g., hospitalization, another outpatient clinic, etc.).

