### Follow-up

The pregnant women will be followed during all pregnancy period (with one postpartum review) through scheduled visits in every 4 weeks or earlier (according to women necessity), with a minimum of 10 group consultations. The women can come to the hospital other days for laboratory exams, but the attending will always happen in the group.

At each meeting, for each participant, the meeting information will be recorded on an antenatal card, with information like: attendance data, meeting number, gestational age, weight, blood pressure, uterine height, fetal heart rate, fetal movements, fetal presentation, edema, time to return to the clinic, local and professional care. The Control Group (CG) will follow individualized antenatal care according to the service routine, which consists of medical and nursing visits scheduled every 4 weeks or earlier, if necessary.

The data collection process will occur during all antenatal care period. After the inclusion in the research and before starting the antenatal care, the participants (from both groups) will answer a questionnaire about social and demographic questions. Then, will participate in a semi direct individual interview with themes related to women’s expectations about antenatal care and will answer, individually, World Health Organization Quality of Life (WHOQOL brief) [18], State-Trait Anxiety Inventory (IDATE) [19] and Edinburgh [20] scale questionnaires.

Women allocated in intervention group, will participate in focus group also with themes related to women’s expectations about antenatal care, at the first attending of group antenatal care. To evaluate the intervention’s effectiveness, at the finals attending of antenatal care (preferably after 38 weeks of pregnancy) or in postpartum visit, all pregnant women included in the study will answer again the WHOQOL, IDATE and Edinburgh scale questionnaires and a new individual interview will be performed. In all intervention group meetings, pre and post-tests will be carried out on the experience and satisfaction regarding the central theme of each meeting. A new focus group will be performed with both groups (intervention and control).

Women who withdraw or have a medical recommendation to leave IG will be discontinued and these will also participate in an interview with open questions to assess the reasons for giving up on group antenatal care.

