Data about pregnancy, maternal and perinatal outcomes will be assessed by medical record review. Strategies like phone call reminder for each appointment and evaluation of women’s satisfaction will be adopted to improve the adherence in study.

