### Statistical analysis

The quantitative data will be saved in a spreadsheet of Microsoft Excel® Software and will be stored for a five-year period. A descriptive analysis will be conducted using measures of central tendency and dispersion for quantitative variables and frequencies and percentages for categorical variables. The groups and time periods will be compared with regard to quantitative outcomes using the unpaired or paired Student’s t-test, Mann-Whitney test or paired Wilcoxon test, according to the data distribution.

Data distribution will be assessed using the Shapiro-Wilk test. Pearson’s chi-square, Fisher’s exact or McNemar’s tests will be used for categorical outcomes. The Bonferroni correction [23] will be applied to the significance level according to the number of comparisons made for each outcome variable. The significance level was set at 5% and the program *Statistical Analysis System* (SAS), version 9.4 will be used.

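### An intervention-arm-only discontinuation rule, and an untimed exclusion criterion with the same trigger, leave unclear whether women who leave group care stay in the trial

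*Protocol article*

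**What the plan says.** The protocol article's Follow-up section sets a rule for one arm: "Women who withdraw or have a medical recommendation to leave IG will be discontinued". It adds that "these will also participate in an interview with open questions to assess the reasons for giving up on group antenatal care". No matching rule is given for controls, whose care is described as follows: "The Control Group (CG) will follow individualized antenatal care according to the service routine".

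The section on inclusion and exclusion criteria has a single exclusion: "The exclusion criteria is professional indication validated by a professor to individualize care". Such women "will be sent to the indicated professionals or sectors, e.g., hospitalization, another outpatient clinic, etc". It does not say whether this applies only before allocation or also afterwards.

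Two other statements in Follow-up bear on what happens to women who leave the group. On questionnaires: "all pregnant women included in the study will answer again the WHOQOL, IDATE and Edinburgh scale questionnaires". On clinical outcomes: "Data about pregnancy, maternal and perinatal outcomes will be assessed by medical record review".

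The second objective, at the end of the Background, is a between-arm comparison of maternal and perinatal outcomes. The Statistical analysis section says that "The groups and time periods will be compared with regard to quantitative outcomes" and does not describe which women enter that comparison.

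**The concern.** The rule acts after randomisation, names one arm, and has a clinical recommendation as one of its triggers. A control woman who develops the same complication is already in individual care and simply continues. If *discontinued* means discontinued from the study, the intervention arm loses some women with complications and some who disliked the format, while the control arm keeps their counterparts. The Discussion expects less preterm labor, less anxiety and depression and better quality of life with group care. For preterm birth at least, one-sided loss of complicated pregnancies would push the result in the expected direction without any effect of the intervention.

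The exclusion criterion adds to the uncertainty. Its examples, such as admission to hospital or transfer to another clinic, fit events later in pregnancy as well as the situation at entry. The randomisation section goes straight from consent to allocation and mentions no prior check of this criterion.

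Timing matters too. Final questionnaires that are never requested from women who leave cannot be recovered by a later analysis plan.

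**Working it through.** **Plan's own figure.** The only relevant number is 12–15 women per group (Sample size), taken from pilot-study recommendations. It has no effect size, SD, power or dropout rate behind it, so there is nothing to reproduce. It does set the scale: losing three women is 3/15 = 20% or 3/12 = 25% of the arm.

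**Two readings, side by side.**
- *Discontinued from the study.* Leaving IG is the trigger and discontinuation is the consequence, so the sentence says little unless the consequence goes further than the trigger. The only data collection tied specifically to these women is the exit interview. The limitations section discusses preference for individual visits under loss to follow-up and non-adherence, and its remedies all promote attendance.
- *Discontinued from group care.* The exit interview is described as something they *also* do. The repeat questionnaires are for all women included in the study. Clinical outcomes come from records, which do not depend on attending the group.

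The text does not decide between them.

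**How likely the rule is to be used.** With an assumed probability p per woman, P(at least one of 15) = 1 − (1 − p)^15. This is 54% at p = 5%, 79% at 10% and 96% at 20%.

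**Binary outcome, no true effect.** Let q be the share who trigger the rule (the same in both arms, by randomisation), r1 their risk and r0 the risk in the rest. If they are dropped from IG only:
- control risk = q·r1 + (1 − q)·r0, and IG risk = r0
- spurious difference = −q·(r1 − r0)

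With r0 = 8%, the table gives control risk and spurious risk ratio (RR). All inputs are assumptions.

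| Dropped from 15 | r1 = 16% | r1 = 30% | r1 = 50% |
|---|---|---|---|
| 1 | 8.5%, RR 0.94 | 9.5%, RR 0.85 | 10.8%, RR 0.74 |
| 2 | 9.1%, RR 0.88 | 10.9%, RR 0.73 | 13.6%, RR 0.59 |
| 3 | 9.6%, RR 0.83 | 12.4%, RR 0.65 | 16.4%, RR 0.49 |

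The risk difference runs from −0.5 to −8.4 percentage points. Another assumed set shows how far the result depends on inputs: with r0 = 6%, q = 10% and r1 = 30%, RR = 0.06/0.084 = 0.71; with q = 30% and r1 = 40%, RR = 0.06/0.162 = 0.37.

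**Questionnaire scores, no true effect.** If removed women score d SD worse than the rest, the spurious benefit is q·d. For 1 to 3 of 15 this is 0.03 to 0.10 SD at d = 0.5 and 0.07 to 0.20 SD at d = 1.0. At d = −0.5 (removed women score better) it reverses to −0.03 to −0.10 SD.

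**Effect on the test.** A simulation (20,000 runs, 12 or 15 per arm, two-sided t-test at 5%) dropped the 1 to 3 highest-risk IG women:
- risk uncorrelated with outcome: shift about 0
- correlation 0.3: shift 0.04–0.12 SD, type I error 5.1–6.0%
- correlation 0.6: shift 0.08–0.24 SD, type I error 5.8–8.8%
- nobody dropped: shift about 0, type I error 4.6–5.3%

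For comparison, the difference detectable with 80% power is (1.96 + 0.84)·√(2/n), which is 1.14 SD at n = 12 and 1.02 SD at n = 15 (1.20 and 1.06 SD by the exact t-test).

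**The case against.** The strongest reply is that removal from the data is inferred. The sentence concerns leaving IG, and the interview concerns giving up group care, so ending group sessions is a natural meaning. The other Follow-up statements give a route to these women's outcomes, and nothing says they leave the analysis. The exclusion criterion can be read as an ordinary entry criterion. An analysis-set or intention-to-treat statement may well stand in a fuller protocol or analysis plan that is not shown, so its absence here is not a fault.

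Most of that stands, and it limits the point to an unclear, one-sided rule. It does not remove the point. Whether a discontinued woman still counts as included in the study is exactly what is unclear, and record review shows that clinical data could be obtained, not that they will be used.

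A reader might go further and infer that the highest-risk women are taken out of one arm, that every comparison is biased toward group care, and that randomisation is broken. The document does not support this:
- The same sentence covers any woman who withdraws, and the limitations section expects some to leave by preference.
- The study starts in the clinic where low-risk pregnancies are concentrated.
- Bias is zero if women are compared as allocated, near zero for outcomes unrelated to the trigger, and of either sign for scores.
- The meeting-level satisfaction tests are done in IG only, so there is no between-arm comparison to bias.

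**Conclusion.** The point holds as a rule that needs rewording. After randomisation, and in the intervention arm only, women are discontinued for reasons that include a medical recommendation. An exclusion criterion with much the same trigger has no timing, and the text does not say whether these women leave the sessions or the study.

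If they are dropped, the loss is one-sided and partly risk-related. Clinical outcomes such as preterm birth would then probably tilt toward group care, with a spurious risk ratio between 0.94 and 0.49 in the main illustration. For scores, the shift of up to about 0.24 SD is small beside the 1.06 to 1.20 SD the trial could detect by t-test, and it could go either way. All these sizes rest on assumed trigger rates, risks and correlations, since the document gives none. They describe expected bias, not a result that a pilot of this size could estimate reliably. If women are followed and compared as allocated, this bias does not arise.

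**What to change.** - **Follow-up.** State that discontinuation refers to group sessions only. Women who leave the group for any reason remain in the trial, are asked for the final WHOQOL, IDATE and Edinburgh questionnaires, have their records reviewed as already planned, and are compared in the arm to which they were allocated.
- **Inclusion and exclusion criteria.** State that the indication to individualise care is checked before the envelope is opened and does not remove women already randomised.

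When or why a woman leaves group care remains a clinical decision and is unchanged.

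The cost is wording plus a few extra questionnaires, including from women who have moved to another clinic. Keeping women who left the group in the intervention arm may dilute the estimated effect. The article reports that recruitment had not started, so the change could be made before any woman is affected.

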### Randomization and masking method

After accepting to participate in the research and signing the informed consent form, the researcher will randomly select the assigned group. We will use a computerized randomizer. A random sequence will be generated by a computer software (http://www.random.org/) and will be followed for the allocation of participants into the experimental and control groups. A sealed envelope containing the randomization form previously filled out in the Intervention Group or Control Group, which will be opened and read with the patient.

The study will not be masked, since the pregnant woman and the researcher will know whether the patient belongs to the IG or CG.The Intervention Group (IG) is going to be composed by a maximum of 15 pregnant women. The group will be attending in 11 meetings with approximately two-hour duration each, every 4 weeks or earlier, if necessary, with the following themes discussions:

Nutrition and physical activity during pregnancy; Most common management complaints and signs of complications; Social and social security rights and mental health; Reproductive planning and sexuality; Childbirth preparation guidelines, warning signs and maternity visit; Breastfeeding; Gestational complications and preparation for trousseau; Cognitive and physical development of the child; Nutrition in the fourth quarter; Postpartum follow-up routines and group closure.

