### Procedures and techniques

The procedures will be done by the research team. The physical exams will be performed by an obstetrics nurse or obstetrics medical doctor that will participate in the group during all attending period. While a woman is in physical exam, the others will take turns with the responsibility of evaluate and write their own weight and blood pressure (using digital device confirmed by the medical team). After the physical exam, the women will be able to make questions and participate in the group discussion. Although the themes were previously chosen for each meeting, the group will be conducted according to women necessity and other themes can arise.

The final interviews among focus groups and questionnaires will be performed by a researcher that did not participate in the group.

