### Quality control

Procedures will be adopted for quality control, such as: subject identification numbers to prevent data loss or confusion; review of completed forms, organization of instruments, and verification of the coding of textual responses; data will be entered into the database by two different data entry clerks to avoid data loss or typing errors.

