### Reports the status and timeline of the study

A) initial training for the intervention team will be held in March and June 2025; B) participant recruitment has not started and is scheduled to take place between May 01 and June 30, 2025; C) data collection will be completed by January, 2026; D) Qualitative data analysis and validation with peer researchers, using NVIVO14 and Quantitative analysis with support from the university’s statistics service and E) results are expected by March, 2026.

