## Potential limitations and mitigation strategies

The main potential biases of the study are those commonly associated with randomized clinical trials. During the discussions on the study design, several precautions were taken to minimize the risks, as outlined below:

Selection bias: To minimize this risk, we will rely on computer-generated random numbers. Performance bias: To further minimize this, sequentially numbered, opaque, and sealed envelopes will be used. Performance bias: The study will not involve blinding or masking. The authors will discuss potential biases in the process after the completion of the pilot study. Detection bias: There will be no blinding in the outcome assessment, but the authors believe that the outcome cannot be influenced by the lack of blinding.

Some challenges, such as late initiation of prenatal care and the cultural preference for traditional individual prenatal consultations, are anticipated during the recruitment process. To address this, awareness and information about the project will be shared with healthcare professionals to refer women to the project.

Loss to follow-up and participant non-adherence are potential issues, as there may be dropouts or refusals due to the belief that individual consultations are more appropriate, given that this is the traditional model used nationwide. To address this, several strategies will be implemented, including appointment reminders via phone (with patient consent), raising awareness among participants at the end of each session about the importance of the next topic, and reviewing the study objectives at the conclusion of each session.

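### All masking, including of outcome assessment, is waived on an unsupported belief; masked reading of birth and newborn records and coded arms for the analysis are feasible in part and cheap

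*Protocol article*

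**What the plan says.** The Randomization and masking method section declares the trial open and gives one reason: "The study will not be masked, since the pregnant woman and the researcher will know whether the patient belongs to the IG or CG".

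The Potential limitations and mitigation strategies section goes further. It rules out blinding or masking for the study in general and says of bias in detecting outcomes: "There will be no blinding in the outcome assessment, but the authors believe that the outcome cannot be influenced by the lack of blinding". No argument follows. Bias in the process is left for later: "The authors will discuss potential biases in the process after the completion of the pilot study".

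The outcomes come from two kinds of source:

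- **Self-report.** Quality of life, anxiety and depression scales are completed at entry and near the end. For the final round, Procedures and techniques offers a safeguard: "The final interviews among focus groups and questionnaires will be performed by a researcher that did not participate in the group".
- **Records.** Follow-up says "Data about pregnancy, maternal and perinatal outcomes will be assessed by medical record review". It does not say who reads the records or what that person knows about allocation.

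Two other roles appear. Under Quality control, "data will be entered into the database by two different data entry clerks". The timeline section mentions "Quantitative analysis with support from the university’s statistics service".

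**The concern.** Women and carers cannot be masked when one arm meets as a group and the other is seen individually. Two later steps are different: reading delivery and newborn outcomes from the record, and running the comparisons. The reason given for an open trial concerns people who take part in allocation or care, yet the waiver in the limitations section covers every assessment.

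The direction of any bias is foreseeable. The Abstract expects a positive result in the intervention group, and the Discussion names less preterm labor and a trend in early breastfeeding. Classifying such items from a chart can need judgement. A reader who knows the arm and expects a benefit may resolve borderline cases one way without meaning to. Comparing maternal and perinatal outcomes is the second aim in the Background, and the record outcomes are a substantial part of it.

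**Working it through.** The plan gives no figure on this point to reproduce. The check has two parts.

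**1. The sections side by side**

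| Step | What the plan says | Does the stated reason apply? |
|---|---|---|
| Delivering and receiving care | Open, because woman and researcher know the arm | Yes |
| Final questionnaires and interviews | Open, but run by a researcher outside the group | Largely: the woman answers and knows her arm |
| Abstracting birth and newborn outcomes | Open, under the general waiver; abstractor not named | Not for an abstractor without the allocation list |
| Comparing the arms | Support from the statistics service; masking not mentioned | Not for an analyst working with coded arms |

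The plan thus recognises assessor independence for the questionnaires and offers no counterpart for the record outcomes. Independence is also not masking: a researcher who runs the final interviews and focus groups will probably learn the arm.

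**2. How much one classification weighs**

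Input: 12 to 15 participants per group (Sample size), taking group to mean trial arm.

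One woman's share of an arm's rate is 1/n, and two women's share is 2/n:

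- n = 15: 1/15 = 6.7 points; 2/15 = 13.3 points.
- n = 12: 1/12 = 8.3 points; 2/12 = 16.7 points.

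For scale, take a two-sided Fisher exact test (a test named under Statistical analysis) with equal arms of n, no event in one arm and k in the other. Then p = 2 × C(n, k) / C(2n, k).

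| n per arm | 0 versus 4 events | 0 versus 5 events |
|---|---|---|
| 12 | 2 × 495 / 10,626 = 0.093 | 2 × 792 / 42,504 = 0.037 |
| 15 | 2 × 1,365 / 27,405 = 0.100 | 2 × 3,003 / 142,506 = 0.042 |

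At this boundary one coding decision crosses the 5% level, before any Bonferroni correction. The event counts are assumptions chosen to show the boundary. The document gives no event rates or misclassification rates.

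**The case against.** The strongest reply is that this is a small pilot, openly unmasked, whose first aim is implementation. Its stated means of judging effectiveness are the quality of life, anxiety and depression scales, which masked abstraction would not protect. Clinical staff write the records during care, so arm-aware charting has happened before anyone abstracts a page. Some birth outcomes leave little room for judgement. The arithmetic on one woman holds for any study of this size and is not evidence of bias.

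All of that stands and limits the gain. It does not supply the missing reason for saying that the outcome cannot be influenced. The self-reported scales make that statement harder to defend.

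A reader might also infer more than the document supports:

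- **That masking would cost nothing with existing staff.** The clerks are described only as entering data. Abstraction would be an added task, and someone must separate the delivery and newborn pages.
- **That the analysts will certainly know the arms.** The general waiver excludes masking, but nothing describes what the statistics service will see, and details could stand in a plan not shown. This part is secondary.
- **That the second aim rests wholly on records.** Maternal outcomes can include the self-report scales.
- **That tests and corrections are chosen freely after seeing the data.** Statistical analysis fixes a rule: the Shapiro-Wilk test guides the choice of test, and Bonferroni follows the number of comparisons per outcome.
- **That complications are a named outcome needing judgement.** They appear as a meeting theme. Preterm labor and breastfeeding appear as expectations in the Discussion.

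**Conclusion.** The concern holds in a limited form. The limitations section makes an explicit choice to waive all masking, including of outcome assessment, and rests it on an unsupported belief. The reason given elsewhere covers only the woman and the researcher. The record outcomes have no counterpart to the outside researcher used for the final questionnaires.

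One reclassified woman moves an arm's rate by 6.7 to 8.3 points, assuming 12 to 15 women per arm with outcome data. That measures how exposed the results are; it does not estimate a bias. The change is worth making because it is cheap and removes some avoidable detection and analysis bias. It cannot remove bias from self-report or from clinicians' own entries.

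**What to change.** 1. In Potential limitations and mitigation strategies, delete the belief that lack of blinding cannot influence the outcome. State that the self-reported scales remain open to bias from the open design.
2. State who abstracts the birth and newborn outcomes: a team member already in the plan who did not deliver the groups and does not hold the allocation list. The researcher who runs the final interviews is a weaker choice, being likely to know the arms. Fix the outcome definitions beforehand and supply only the delivery and newborn pages, under study numbers.
3. Give the statistics service a data set with arms coded A and B. Keep intervention-only variables, such as the meeting pre- and post-tests, in a separate file, and reveal the code once the planned comparisons have been run.
4. Limit the general waiver of masking to the women, the carers and the assessments that cannot be masked.

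**Cost:** a small added abstraction and file-handling task, with no extra participants or visits. **Limit:** the masking is partial. Antenatal pages can reveal the arm (the intervention group's card carries the meeting number), and clinicians' entries may already reflect it.
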